### Data inputting

Data will be input into a flat SPSS spreadsheet by the trial co-ordinator. All primary data (GHQ and WSAS) at all time points will be double entered by an administrator. This will then be checked for errors and discrepancies, which will then be corrected by consulting the raw questionnaire data (paper based or online). A percentage of all other data inputting will also be double entered to ensure accuracy. Any follow-up action (e.g. double entry of more data) will be taken as necessary.

#### Qualitative interviews

On receipt of completed post-therapy questionnaires, details of those participants who have consented to take part in the in-depth interview will be passed to a post-doctoral researcher who has not had any involvement in other aspects of the trial.

Around 15 CBT participants and 15 SL participants will be interviewed regarding their experiences of therapy. If a large enough pool of consenting participants is available, purposive sampling will be employed on the basis of questionnaire-based reports of therapy satisfaction, perceived improvement, and demographic and illness characteristics.

The interviewer will contact each participant to schedule a telephone interview and conduct the interview according to an interview schedule. Questions address expectations of therapy, experiences of therapy sessions, features of therapy liked and disliked, and the process of change (or not) as a result of therapy. Each interview will be audio-taped or digitally recorded. Interviews will be transcribed by an administrator, omitting any information that may compromise confidentiality. Completed recordings and transcripts will be stored in a locked cabinet (if printed) or in a password protected file (if digital) for analysis after the trial has concluded.

#### Independent monitoring and quality control

A Trial Steering Committee (TSC) including a Data Monitoring Group has been set up to monitor the conduct of the trial. They will provide overall supervision for the trial and safeguard its integrity. Authority for continuation of the trial lies with the TSC. The committee includes an independent chairperson, the lead and principal investigators, the trial co-ordinator, a statistician, a representative from the MS Society and a patient representative. The committee will meet at least annually during the trial period, and more frequently and/or via telephone conference or email communication if pressing issues arise.

#### Compliance

The trial will be conducted in compliance with the Declaration of Helsinki, MRC Good Clinical Practice (GCP) guidance, the Data Protection Act (1998), the National Research Ethics Service (NRES) approvals, NHS Trust regulations, and other regulatory requirements as appropriate. The final trial publication will include the items recommended under the extended CONSORT statement for randomized trials of nonpharmacologic treatment [53].

#### Participant safety

Both CBT and SL are expected to be of low risk to participants. They are non-invasive talking therapies and similar interventions have been previously used in chronic illness populations. If the nurses are concerned about a patient's safety, particularly if they believe the person may be vulnerable to self-harm, they immediately contact one of the therapy supervisors who will telephone the patients to assess the severity of the situation. If necessary, a referral will be made to ensure the patient gets the support they need.

#### Adverse events/reactions

Adverse events (AE), adverse reactions (AR), serious adverse events (SAE) and serious adverse reactions (SAR) will be defined according to the usual clinical trial definitions. Where these occur they will be recorded on the trial spreadsheet and reported to the appropriate authorities and followed up in the standard manner.

#### Stopping/discontinuation rules

Departures from the trial protocol, changes to the manualized treatments, and breaking of the randomization code will only occur with the advice of the TSC if it becomes apparent that a particular treatment arm is causing a consistent pattern of deterioration, or if there is another obvious and significant clinical necessity.

#### Withdrawals from therapy

If a participant expresses the wish to withdraw from the trial, the nurse-therapist will contact the participant to ascertain the reason for drop-out if the participant is willing to share this. They will be offered the option of talking to a principal investigator instead if they wish. If the participant considers that they are deteriorating a principal investigator will contact them and discuss an appropriate solution.

The nurse-therapist (or principal investigator if they make contact) should ascertain whether consent is withdrawn from:

a) further treatment only

b) further treatment and follow-up (questionnaires plus the in-depth telephone interview)

c) retaining data already collected for use in final analysis.

The reason for withdrawal (e.g. adverse events, relapse, illness progression, inability to adhere, inability to attend) will be communicated to the principal investigator for that centre as well as the trial co-ordinator who will record and report this information as appropriate.

If it is felt that a participant should be withdrawn from the trial this will be discussed with the nurse-therapist, principal investigator and clinical supervisor. One of the principal investigators will assess the participant clinically within a week and arrange appropriate ongoing care. The nurse-therapist will write to the participant's GP and MS service to confirm withdrawal from treatment.

#### Statistical analysis plan

Statistical analysis will be carried out in SPSS and/or Stata general purpose statistical analysis packages. Mediation modeling may require use of specialist structural equation modeling software (e.g. AMOS or M-Plus).

All treatment group comparisons will be carried out on an intention-to-treat basis, that is subjects will be analyzed in the group to which they were randomized irrespectively of the treatment received. The primary and secondary longitudinal outcomes will be analyzed using linear mixed modeling. In these models the outcome variable at the post-treatment time points will be the dependent variable and baseline values of the outcome variable, centre, time (post-treatment, 6 M follow-up or 12 M follow-up), group (CBT or Supportive Listening) and a time × group interaction terms will feature as explanatory variables. To account for correlation between measures taken on the same individual at various time points subject-varying random intercepts and slopes of time will also be included in the model. Further baseline variables might be used as explanatory variables, to provide more powerful group comparisons if they are found to be predictive of the outcome variable. As the model fitting will by maximum likelihood such analyses are valid if missing data arises at random (MAR). The effect of informative missingness processes will be explored by means of a formal sensitivity analysis [54].

We will further investigate whether results were unduly influenced by patients who have shown marked disease progression during the trial or who have altered medication during the trial period. We will also assess the sensitivity of the results to excluding patients who did not receive a sufficient number of treatment sessions or those who had low expectations of the therapy they received.

An approach similar to Baron and Kenny's mediation modeling [55]will be used to explore whether change of psychological outcomes mediates the path from therapy to change in MS adjustment. Specifically we will use instrumental variable methods advocated by Dunn and colleagues to try and adjust for unobserved confounders of the path from mediations to outcomes [56,57].

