#### Baseline questionnaire assessments

Eligible participants will be sent the baseline questionnaire and freepost return envelope together with a copy of their consent form. The schedule of assessments in the baseline questionnaire and subsequent follow-up questionnaires is outlined in Table 1.

**Table 1 T1:** Details and schedule of saMS trial assessment procedures

Measures administered	Baseline (week 0)	Mid-therapy (week 5)	Post-therapy (week 15)	6 month follow-up (week 26)	12 month follow-up (week 52)
Demographics	X	-	-	-	-

Detailed MS questions-(date of diagnosis, time since symptoms started, type of MS, recent and current relapses, treatment for depression, supplements or alternative therapies, participation in MS organizations)	X	-	-	-	-

Brief MS questions (recent changes in medication, interventions, recent and current relapses)	-	-	X	X	X

Expectations/preferences for therapy	X	-	-	-	-

Global improvement and satisfaction ratings	-	-	X	-	-

Feedback on CBT manual/strategies	-	-	X	-	-

Continuation of use of CBT	-	-	-	X	X

General Health Questionnaire (GHQ-12 [41])	X	X	X	X	X

Work and Social Adjustment Scale (WSAS [43])	X	X	X	X	X

Beliefs about Emotions Scale (BES; Rimes & Chalder; in preparation)	X	X	X	X	X

Significant Others Scale (SOS [49])	X	-	X	X	X

Acceptance of Chronic Health Conditions Scale (ACHC [45])	X	X	X	X	X

Psychological Vulnerability Scale (PVS [46])	X	X	X	X	X

Brief Illness Perception Questionnaire (B-IPQ [48])	X	X	X	X	X

Cognitive and Behavioural Responses to Symptoms Questionnaire (CBRSQ; Moss-Morris, Chalder, Skerrett & Baldwin, in preparation)	X	X	X	X	X

Client Service Receipt Inventory (CSRI [51])	X	-	-	X	X

EuroQoL (EQ5D [44])	X	-	-	X	X

Self-report Expanded Disability Status Scale (EDSS [50])	X	-	-	-	X

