#### Outcome assessments

Questionnaires (see Table 1) will be completed at baseline (prior to randomisation), mid-therapy (session 5 of therapy sessions), post-therapy follow-up (15 weeks after randomisation), 6 month follow-up (26 weeks after randomisation) and 12 month follow-up (52 weeks after randomisation). All assessments are questionnaire-based. Data collection will be managed by the trial co-ordinator who will be blind to treatment allocation. Participants will be able to choose whether to complete online or paper-based questionnaires (returned by freepost). Dates that questionnaires are sent out and received will be recorded. A reminder phone call or reminder emails will be used if the questionnaire is not received within two weeks of send-out. After four weeks another copy of the questionnaire pack will be reissued.

If participants are unable to complete questionnaires themselves (e.g. due to relapse) the trial co-ordinator will go through the questionnaire on the telephone and this will be logged as such on the trial database. Spouses/partners/friends will not be allowed to complete the questionnaire on the participant's behalf or assist them with writing their answers. Completed, returned questionnaires will be checked by the trial co-ordinator and participants contacted if there is a large amount of missing data.

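### Week-5 GHQ and WSAS are collected but kept out of the outcome model, so the missing-at-random assumption is less plausible than it could be

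*Protocol article*

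**What the plan says.** In Table 1 (Baseline questionnaire assessments), the rows "General Health Questionnaire (GHQ-12 [41" and "Work and Social Adjustment Scale (WSAS [43" are marked at all five occasions: baseline and weeks 5, 15, 26 and 52. ACHC and PVS are also marked at all five; EQ-5D is not marked at week 5. Outcome assessments describes the second occasion as "mid-therapy (session 5 of therapy sessions", which falls after randomisation. Data inputting has GHQ and WSAS double-entered at every time point.

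The Statistical analysis plan section then fixes the model. It states that "the outcome variable at the post-treatment time points will be the dependent variable", and it lists the levels as "time (post-treatment, 6 M follow-up or 12 M follow-up". Baseline value, centre, group and time × group are the other terms, with random intercepts and random slopes of time. On additional covariates it says that "Further baseline variables might be used as explanatory variables". Fitting is by maximum likelihood, and "such analyses are valid if missing data arises at random (MAR". A formal sensitivity analysis for informative missingness is also planned. The Abstract places the primary outcomes at 12 months.

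**The concern.** Week 5 enters the outcome model neither as a response nor as a covariate. The time levels are enumerated, so this is a stated choice and not a detail left open.

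Two things follow. First, a participant with baseline and week-5 scores but nothing at weeks 15, 26 or 52 has no row in the model. Second, maximum likelihood is valid under missingness that is at random given the data in the model. If leaving between weeks 5 and 15 depends on distress or impairment at week 5, missingness is at random when week 5 is included and in general is not when it is left out.

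Arm-specific drop-out is possible. CBT sets tasks between sessions and SL prohibits them, and Withdrawals from therapy gives inability to adhere as an example of a reason for leaving. What is at stake is a small bias in the 12-month CBT–SL contrast that data already in hand could reduce.

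**Working it through.** **Inputs from the protocol.** Effect 0.60 SD; alpha 0.025 per primary outcome; power 80%; 55 per arm evaluable; attrition about 10%; 61 per arm randomised (122 in total); 3/72 = 4% lost in the team's earlier fatigue trial.

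**The plan's own figure.** A two-sample t-test with d = 0.60, two-sided alpha 0.025 and 80% power needs 54.08, so 55 per arm, as stated. 55/0.9 = 61.1, in line with the stated 61. Nothing below changes the sample size.

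**How many could be affected.** 122 × 0.10 = 12.2 and 122 × 0.04 = 4.9. So about 5 to 12 participants would be lost at follow-up in all. The protocol does not say how many of them would leave between weeks 5 and 15.

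**Assumptions not in the protocol.** Correlation 0.55 between any two occasions (other sets between 0.5 and 0.7 also tried); drop-out log-odds of 1.0 per SD of the last observed score.

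**Approximate bias, all losses between weeks 5 and 15.** Let p be the proportion lost in an arm, β the log-odds per SD, and ρ the common correlation. Given baseline, the covariance of the week-5 and week-52 scores is ρ − ρ². Completers in an arm where drop-out rises with the week-5 score are shifted at week 52 by about

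bias ≈ p/(1 − p) × β × (ρ − ρ²)

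- 10% lost, one arm only: 0.111 × 1.0 × (0.55 − 0.3025) = 0.111 × 0.2475 = 0.027 SD.
- 10% lost, opposite directions in the two arms: 2 × 0.027 = 0.055 SD.
- 4% lost: 0.0417 × 0.2475 = 0.010 SD, and 0.021 SD for opposite directions.
- Same dependence in both arms: the shifts cancel, so about 0.

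The approximation runs slightly high, because it treats the drop-out odds as a probability.

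**Simulation of the same cases** (absolute bias in SD at week 52, week 5 omitted):

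| Attrition and timing | Dependence in one arm | Opposite by arm | Equal in both arms |
|---|---|---|---|
| 10%, all in weeks 5–15 | 0.02–0.03 | 0.04–0.06 | about 0 |
| 10%, spread evenly over the three intervals | 0.006–0.007 | 0.014–0.015 | about 0 |
| 4%, all in weeks 5–15 | about 0.01 | about 0.02 (0.025 at most over the correlation sets) | about 0 |
| 4%, spread evenly | 0.004 | 0.006 | about 0 |

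The spread rows are about a third of the early-loss rows (0.024/3 = 0.008; 0.044/3 = 0.015). Later leavers have a week-15 or week-26 score in the model, so the likelihood already conditions on it. With week 5 included, the bias was about zero in the early-loss cases.

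**Precision.** At N = 122 and 10% attrition the standard error with week 5 was 0.98 to 1.00 times that without it (for example 0.1666 against 0.1672).

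**Effect on the error rate, two-sided 2.5% (critical value 2.24), SE 0.165.** Worst case: 0.06/0.165 = 0.36, giving P(Z > 1.88) + P(Z < −2.60) = 0.030 + 0.005 = 3.5%. Losses spread, opposite directions: 0.015/0.165 = 0.09, giving P(Z > 2.15) + P(Z < −2.33) = 0.016 + 0.010 = 2.6%.

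**The case against.** The strongest reply is that this is a coherent design choice. The endpoint is at 12 months, baseline-adjusted modelling of post-treatment scores is standard, and the in-therapy measurements have a purpose in the study of mechanisms of change. That stands as far as it goes: nothing is misstated. But using week 5 for mechanisms does not stop it from also supporting the outcome model.

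Three stronger readings are tempting, and the protocol does not support them.

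- A reader might infer a breach of intention to treat from "All treatment group comparisons will be carried out on an intention-to-treat basis". The same sentence defines this as analysis in the randomised group whatever treatment was received. It does not promise that every participant supplies a response.
- A reader might infer that everyone who leaves therapy is lost. Withdrawals from therapy separates stopping treatment only from stopping treatment and follow-up. The first group still receives questionnaires, and Outcome assessments adds reminders, a reissued pack and telephone completion.
- A reader might infer that adding week 5 removes the bias in general. It does so where drop-out depends on recorded scores, as the simulations assumed. If leaving depends on later, unrecorded distress, bias remains.

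It is also fair that the larger figures place all attrition between weeks 5 and 15, whereas Sample size calculation gives 10% as the total loss at follow-up. They are upper values. The planned sensitivity analysis is a real safeguard, but it addresses missingness that the data cannot explain. It does not replace conditioning on a score that was observed.

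**Conclusion.** The point holds as an optional improvement of small, conditional value. The model leaves out a post-randomisation measurement of both primary outcomes that could make its missing-data assumption more plausible.

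The 12-month bias depends on drop-out related to the week-5 score differing by arm, which the protocol neither shows nor excludes. If it does differ, the bias is at most about 0.06 SD, or 10% of the 0.60 SD design effect (0.06/0.60), and only with 10% attrition, all of it early and in opposite directions by arm. With losses spread over follow-up it is about 0.01 SD, against a standard error of about 0.165 SD. At the 4% attrition of the team's earlier trial it is about 0.02 SD or less at a correlation of 0.55. If the dependence is equal in both arms it is about zero. The correlations, the drop-out slope and the timing of losses are assumptions. No gain in precision worth counting should be expected.

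**What to change.** Before the group codes are broken, amend the model so that week 5 is a fourth level of categorical time with its own time × group term. Use an unstructured covariance across the four occasions in place of the random intercept and linear slope, which may fit poorly when an on-treatment occasion is added. Keep the week-52 CBT–SL contrast as the primary estimate, report week 5 descriptively, and keep the planned sensitivity analysis for informative missingness. The same change suits ACHC and PVS; it does not apply to EQ-5D, which has no week-5 measurement.

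The cost is a change of analysis wording and a few extra covariance parameters, with no new data. One drawback should be noted: the mid-therapy occasion is tied to session 5, and Missed or postponed sessions allows the schedule to move, so its timing will vary between participants.

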**Methods/Design:**

This is a two arm randomized multi-centre parallel group controlled trial. 122 consenting participants who meet eligibility criteria will be randomly allocated to receive either Cognitive Behavioral Therapy or Supportive Listening. Eight one hour sessions of therapy (delivered over a period of 10 weeks) will be delivered by general nurses trained in both treatments. Self-report questionnaire data will be collected at baseline (0 weeks), mid-therapy (week 5 of therapy), post-therapy (15 weeks) and at six months (26 weeks) and twelve months (52 weeks) follow-up. Primary outcomes are distress and MS-related social and role impairment at twelve month follow-up. Analysis will also consider predictors and mechanisms of change during therapy. In-depth interviews to examine participants' experiences of the interventions will be conducted with a purposively sampled sub-set of the trial participants. An economic analysis will also take place.

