### Participants

#### Sample size calculation

Since there were no available MS CBT trials using either of our primary outcomes we computed a power analysis calculation based on a recent CBT trial for depression in people with MS, which used the Beck Depression Inventory (BDI) as the primary outcome [28]. The BDI, like the GHQ (one of our primary outcomes) is a measure of affective distress. Using a conservative estimate for the within-group standard deviation the effect size from this study was .60. To achieve 80% power at alpha = 0.025 significance level (to adjust for two primary outcomes) we would need 55 patients in each group to detect an effect of this magnitude by an independent samples t-test. To allow for attrition of around 10% at follow-up we need to initially include 61 participants in each group. In our CBT for MS fatigue trial we only lost 3/72 patients to follow-up (4%).

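### The outcome model applies one baseline coefficient at weeks 15, 26 and 52; a baseline × time term would protect the precision of the 12-month contrast if the baseline correlation changes over follow-up

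*Protocol article*

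**What the plan says.** The Statistical analysis plan section of the protocol article gives the explanatory variables of the linear mixed model as "baseline values of the outcome variable, centre, time (post-treatment, 6 M follow-up or 12 M follow-up), group (CBT or Supportive Listening"), and adds that "a time × group interaction terms will feature as explanatory variables". For within-person correlation, "subject-varying random intercepts and slopes of time will also be included in the model". It also leaves room for more covariates: "Further baseline variables might be used as explanatory variables, to provide more powerful group comparisons", if they turn out to be predictive.

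The Abstract fixes the deciding visit: "Primary outcomes are distress and MS-related social and role impairment at twelve month follow-up". The Outcome assessments section places the modelled visits at "post-therapy follow-up (15 weeks after randomisation), 6 month follow-up (26 weeks after randomisation) and 12 month follow-up (52 weeks after randomisation").

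**The concern.** The time × group term lets the treatment effect differ by visit. Nothing listed does the same for the baseline score, so one baseline coefficient is estimated from all three visits and applied at each. The random intercepts and slopes describe how individuals scatter around the fixed part; they do not let the fixed baseline coefficient differ by visit. The clause on further baseline variables concerns additional covariates and names no interaction of baseline with time.

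Two of the three visits fall in the first half of the follow-up year. If baseline GHQ or WSAS predicts week 15 better than week 52, the shared coefficient is larger than the one that suits week 52; if prediction improves with time, it is smaller. In either case the 12-month contrast is less precise than the collected data allow. A chance baseline difference between the arms is also removed by the wrong amount.

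**Working it through.** **The plan's own figure.** The Sample size calculation section says "Using a conservative estimate for the within-group standard deviation the effect size from this study was .60" and "To achieve 80% power at alpha = 0.025 significance level (to adjust for two primary outcomes"), and arrives at 55 per group with an unadjusted t-test. The normal approximation, two-sided, gives 2 × (2.241 + 0.842)² / 0.60² = 52.8, so 53. The exact t-test gives 54.1, so 55, with power 80.7% at 55. The figure is reproduced. It takes no credit for baseline adjustment.

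**Formula.** Standardise the outcome to SD 1 at every visit. Let r15, r26 and r52 be its correlations with baseline and b the shared coefficient. With complete data, and after adjustment for centre, the week-52 contrast is the difference at week 52 minus b times the difference at baseline. Its variance is proportional to 1 − 2·b·r52 + b². The minimum, 1 − r52², is reached at b = r52. Hence

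variance ratio = 1 + (b − r52)² / (1 − r52²).

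A baseline difference of 0.2 SD shifts the estimate by (b − r52) × 0.2, in size. At 55 per group a difference at least that large has probability 2Φ(−0.2/√(2/55)) = 0.29.

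**Inputs that must be assumed.** The documents give no correlation between baseline and any later visit. The scenarios below are assumptions. For each, b is the generalised least squares pooled slope, b = 1′Wr / 1′W1. Here W is the inverse of V + dd′, V is the between-visit correlation matrix minus rr′, and d = r − b; the equation is iterated to convergence. The assumed correlations between follow-up visits (15–26, 26–52, 15–52) are in the second column.

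| r15/r26/r52 | between visits | b | variance ratio | SE increase | shift at 0.2 SD | power, visit-specific → shared |
|---|---|---|---|---|---|---|
| .5/.5/.5 | .70/.70/.65 | 0.500 | 1.000 | 0% | 0 | 91.1% → 91.1% |
| .6/.55/.5 | .70/.70/.60 | 0.557 | 1.004 | 0.2% | 0.011 | 91.1% → 91.0% |
| .6/.5/.4 | .70/.65/.55 | 0.521 | 1.017 | 0.9% | 0.024 | 87.5% → 86.9% |
| .7/.55/.4 | .75/.65/.55 | 0.606 | 1.050 | 2.5% | 0.041 | 87.5% → 85.8% |
| .7/.5/.3 | .70/.60/.45 | 0.580 | 1.086 | 4.2% | 0.056 | 84.6% → 81.2% |
| .4/.5/.6 | .70/.65/.55 | 0.526 | 1.009 | 0.4% | 0.015, opposite direction | 95.0% → 94.8% |

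Worked line for .6/.5/.4: (0.521 − 0.40)² / (1 − 0.16) = 0.0146 / 0.84 = 0.017. In patients this is 55 × (1 − 1/1.0173) = 0.9 per arm. The very steep line gives 55 × (1 − 1/1.0859) = 4.4 per arm.

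With b taken as the plain mean of the three correlations, the losses are smaller. The variance is then 1.2% larger for .6/.5/.4, 2.7% for .7/.55/.4 and 4.4% for .7/.5/.3. Over a wider set of 45 assumed declining structures the variance loss was about 0.2–6%, mostly 1–3%.

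**Simulation of the stated model** (250 runs per scenario, 55 per arm, true effect 0.60, random intercept and slope, maximum likelihood):

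- .6/.5/.4: mean estimate 0.61 without and 0.61 with baseline × time; empirical SE 0.168 against 0.167; mean model SE 0.176 against 0.174.
- .7/.5/.3: mean estimate 0.61 and 0.61; empirical SE 0.176 against 0.173; mean model SE 0.192 against 0.184.

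The Monte Carlo error of a mean is about 0.168/√250 = 0.011, so neither model shows bias. The shared coefficient came out at 0.51 and 0.56, against week-52 values of 0.40 and 0.30.

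**Against no adjustment.** Relative to an unadjusted variance of 1, the shared-coefficient variance ran from 0.65 to 0.99 across the scenarios. It was never worse than the analysis on which the trial was sized.

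**The case against.** A mixed model with a common baseline coefficient is a valid and familiar choice, and nothing in the article contradicts it. The article condenses a fuller plan that is not shown and that may contain the interaction. The trial was sized without baseline adjustment, so any precision gained is a bonus. The contrast formula is also exact only with complete data. With about 10% attrition expected and a maximum likelihood fit, earlier visits also inform the week-52 estimate.

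Most of this stands, and it limits the size of the point. It does not remove the point, because the article states the model's terms and they give one baseline coefficient for all visits.

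A reader might infer more: that the adjustment at 12 months is in fact too strong. The documents do not support that. The Background describes the symptoms and course of MS as variable, but this says nothing on how well an early GHQ or WSAS score predicts a later one. With constant correlations there is no effect, and with rising ones the direction reverses.

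A reader might also infer that the treatment estimate is biased. It is not biased over randomisation. The shift arises only given the baseline difference that happens to occur, and it averages to zero.

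**Conclusion.** The point holds as a small, conditional one. The stated model shares one baseline coefficient across the three visits, which is not the best for the 12-month contrast unless the baseline correlation is constant. If the correlation declines, the loss at week 52 is typically 1–3% in variance, or about 0.5–1.5% in standard error. Steep declines cost 4–6% in variance, and a very steep one (0.7/0.5/0.3) about 4% in standard error. A 0.2 SD chance imbalance moves the estimate by about 0.01–0.05 SD against a design effect of 0.60, with 0.056 in the very steep case. Planned power is not breached: the lowest value found was 81.2%. All these sizes rest on assumed correlations and on the complete-data formula. This is a cheap refinement, not the repair of a demonstrated defect.

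**What to change.** Prespecify a baseline × time interaction, with time as a three-level factor, in the mixed models for the primary and secondary outcomes. The 12-month contrast then uses its own baseline coefficient, whichever way the correlations move. Centre the baseline score so that the group effect at each visit stays easy to read. If the full analysis plan already contains the term, nothing further is needed.

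The cost is two extra parameters per outcome, a negligible loss of degrees of freedom and no new data. The quantity being estimated does not change. Naming the term in advance is also cleaner than deciding on it after seeing which baseline terms are predictive.

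### For the three follow-up visits the protocol's random intercepts and slopes leave the week-52 standard error dependent on how time is coded and whether the effects correlate; an unstructured covariance would remove that dependence cheaply

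*Protocol article*

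**What the plan says.** The Statistical analysis plan section of the protocol article fixes the method: "The primary and secondary longitudinal outcomes will be analyzed using linear mixed modeling". The dependent variable is the outcome at the post-treatment visits. Baseline and centre are covariates, and the remaining fixed terms are "time (post-treatment, 6 M follow-up or 12 M follow-up), group (CBT or Supportive Listening) and a time × group interaction terms". Within-person correlation is handled by one statement: "subject-varying random intercepts and slopes of time will also be included in the model". On estimation the section says "As the model fitting will by maximum likelihood such analyses are valid if missing data arises at random (MAR").

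Outcome assessments gives the timing of the modelled visits: "post-therapy follow-up (15 weeks after randomisation), 6 month follow-up (26 weeks after randomisation) and 12 month follow-up (52 weeks after randomisation"). The abstract sets the primary time point: "Primary outcomes are distress and MS-related social and role impairment at twelve month follow-up". Sample size calculation sets the error rate and power: "To achieve 80% power at alpha = 0.025 significance level (to adjust for two primary outcomes"). The random part of this model therefore determines the standard error of the confirmatory comparison at week 52 for both primary outcomes.

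**The concern.** Three visits give a 3×3 within-person covariance with six free elements. Random intercepts and slopes impose a pattern on those six elements, and the pattern depends on two things that the wording leaves open: whether time in the random part is a number or a three-level factor, and whether intercept and slope may correlate. If time is a number and the effects are uncorrelated, the choice of time zero also matters.

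All these readings satisfy the text but do not give the same week-52 standard error. At stake is power in a trial sized to about 80% with no margin, and the possibility that the analyst settles the structure, or replaces it after a failed or boundary fit, once data are in hand.

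**Working it through.** **The plan's own figure.** Inputs from Sample size calculation: effect 0.60 SD, alpha 0.025 (two-sided reproduces the figure), power 80%. The normal approximation is n = 2(2.241 + 0.842)²/0.60² = 52.8, so 53 per arm. The noncentral t gives 55 per arm (power 80.7%), as stated. Attrition: 55/0.9 = 61.1, stated as 61. The stated size is reproduced.

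**Parameter count**, from Σ = ZGZ′ + σ²I, against 6 covariance elements:
- Linear slope, correlated with intercept: 3 + 1 = 4 parameters, rank 4. Identified.
- Three-level factor, uncorrelated effects: 3 + 1 = 4 parameters, rank 4. Identified.
- Three-level factor, unstructured random effects: 6 + 1 = 7 parameters, rank 6. One too many. Only the split between random-effect and residual variance is undetermined; Σ itself is in effect unstructured, so the week-52 contrast and its standard error are unharmed.

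**Effect on the week-52 standard error.** The documents give no variances or correlations for GHQ or WSAS, so the covariances below are assumptions. Setting: 55 per arm, complete data, group-by-visit means, no baseline or centre adjustment, linear time with week 15 as zero. The contrast is then the difference in week-52 means under every structure; only its standard error changes. Let r be the large-sample ratio of model to true standard error. Actual alpha is 2Φ(−2.241r) and power is Φ(0.60·√(55/2) − 2.241r) = Φ(3.146 − 2.241r). At r = 1 these are 2.5% and 82%.

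| Assumed true covariance | r, correlated | r, uncorrelated |
|---|---|---|
| Equal correlation 0.6 | 1.000 | 1.000 |
| Linear slope, variance 0.1 | 1.000 | 1.000 |
| Linear slope, variance 0.3 | 1.000 | 1.000 |
| Correlation 0.8 per 11 weeks, decaying | 1.003 | 1.202 |
| 0.3 shared plus 0.7 decaying (0.7 per 11 weeks) | 1.001 | 1.160 |
| Equal correlation, week-52 SD × 1.3 | 0.984 | 0.946 |
| Equal correlation, week-26 SD × 1.3 | 1.073 | 1.109 |

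A second set of assumed covariances gave 0.99 to 1.06 (correlated) and 0.98 to 1.18 (uncorrelated).

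Worked case, r = 1.202: alpha = 2Φ(−2.694) = 0.7%; power = Φ(3.146 − 2.694) = Φ(0.452) = 67%. Moving only the zero of time from week 15 to randomisation brings r down to 1.09: power = Φ(3.146 − 2.443) = Φ(0.703) = 76%. With correlated effects a shift of origin changes nothing.

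**Simulation** of maximum-likelihood fits in the same seven settings: 1,800 trials each, Wald test at two-sided 0.025, Monte Carlo error about 0.4 points on the type I error.

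| Structure | Type I error | Power at 0.60 SD |
|---|---|---|
| Linear slope, correlated | 1.8–3.5% | 79–84% |
| Linear slope, uncorrelated, decaying correlation | 0.7–1.2% | 71% |
| Unstructured 3×3 | 2.1–3.3% | 81–84% |

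Boundary fits with correlated effects, in the row order of the first table: 51%, 28%, 7%, 0%, 0%, 13% and 98%.

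**Maximum likelihood.** With an unstructured covariance and a normal reference, actual alpha is 2P(t₁₀₈ > 2.241√(108/110)) = 2.8% against 2.5%.

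**The case against.** The strongest case against is that random slopes of time ordinarily means a numeric slope with correlated intercept. That model is standard and identified, and it performs almost as well as the alternative. The bracketed visit list describes the fixed term and does not make the random slope a factor. Coding, random-effects covariance, degrees of freedom and a fallback are commonly left to a full analysis plan, which is not shown.

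Much of this stands. The missing detail is not itself a fault. What remains is that the article states random intercepts and slopes as the chosen structure, and for three fixed visits an alternative exists that needs none of those details.

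A reader might infer more than the documents support:
- That the model cannot be fitted. Over-parameterisation needs both a factor slope and fully unstructured random effects, and even then the contrast is not biased; the risk is a convergence warning or failure.
- That the fit will often land on a zero variance and so be wrong. The rate ran from 0% to 98% depending on assumed covariances. A boundary fit reduces to a simpler model: with equal correlation about half the fits were on the boundary, yet type I error was 1.8%.
- That maximum likelihood undermines the test. The effect is about 0.3 points, and the article cites it to support validity under missing at random.

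**Conclusion.** The point holds as a cheap improvement, not as a demonstrated threat to the primary test. Under the ordinary reading (linear slope, correlated effects) the week-52 standard error is within about 1 to 2% below and 6 to 7% above the truth, and power is close to that of the unstructured model. The material loss needs two conditions together: uncorrelated effects, which the text permits but does not state, and correlation that decays with time. The standard error is then up to about 18 to 20% too large, mostly at the cost of power (near 70% against about 82%). The error can also run the other way: with a larger week-52 SD the uncorrelated slope gave r = 0.946 and a simulated type I error of 4.0%.

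The sizes rest on assumed covariances, complete data and no baseline or centre adjustment. They illustrate a range and do not bound it.

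**What to change.** For GHQ and WSAS, specify visit as a three-level factor with the group-by-visit terms already planned and an unstructured 3×3 within-person covariance in place of the random effects. Fit by REML with a small-sample degrees-of-freedom correction (Satterthwaite or Kenward-Roger, as the software allows), and read the CBT-minus-SL contrast at week 52 from this model. Keep the random-slope model as a sensitivity analysis, with its time coding and random-effects covariance stated.

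The unstructured form has 6 parameters for 6 elements, so it is identified, and it does not depend on the coding or origin of time. It keeps all three visits, the baseline adjustment and likelihood-based handling of data missing at random. The cost is a sentence or two of wording and two more covariance parameters than the correlated linear slope (6 against 4). That is small when the planned 110 participants with all three visits would supply 330 observations. It should be settled before the data are unblinded.
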